## Methods/design

### Study design and timeline

The intervention is designed as a randomized, controlled, participant-blind, add-on superiority trial with three parallel groups. Block randomization will occur with a 1:1 allocation. All participants will receive a Coping Plan intervention [24]. Participants only randomized to receive the Coping Plan will constitute the TAU control group. The TAU control design was chosen to ensure ethical responsiveness to the needs of all participants. Participants in each of the two treatment arms will additionally receive the FutureU-MH intervention. As the intervention is administered via two sessions each targeting different elements of the future self, treatment groups will follow an AB/BA design to allow for differentiation of session effects.

Participants will be assessed at 5 time points: pre-intervention (prior to randomization and completion of the Coping Plan), post-Coping Plan, pre- and post- each intervention session, and at both 1-week and 3 months follow-up (see SPIRIT figure in Table 1). These methods were in accordance with the Declaration of Helsinki and approved by the Ethics Council of the Max-Planck Gesellschaft.

**Table 1 Tab1:** SPIRIT Figure for FutureU for Mental Health Trial

	Timepoint	− 1	0	t1	t2	**t3**	**f1**	**f2**	
Activity/assessment	Approx. time to complete	Screening and online consent	Baseline assessment	TAU: coping plan	Intervention P1 and pre-post assessments/or interim assessment 1 (Control)	Intervention P2 and pre-post assessments/or interim assessment 2 (Control)	1 week follow-up	3 month follow-up	End of study
Enrollment:									
Pre-screening consent	1 min	X							
Screening	3 min	X							
Informed consent (online)	10 min	X							
Random allocation	N/A		X						
Interventions:									
Coping plan intervention (TAU)	25 min			X					
Self-help intervention (in VR)	30 min				E *or*	E *or*			
Positive future memories intervention (in VR)	30 min				E	E			
Assessments:									
Demographics	5 min		X						
Beck Depression Inventory—II	10 min		X					X	
C-SSRS	5 min		X		X	X	X	X	
Self-efficacy	3 min		X					X	
Self-reported future self and mood	10 min		X		X	X	X	X	
Prospective imagery task	5 min		X					X	
BRIEF-A	15 min		X						
Engagement/embodiment	3 min				E	E			
Feasibility outcomes	N/A								X
Acceptability, feasibility, appropriateness	3 min				E	E			
Intervention use	1 min					E	E	E	

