### Outcomes measures

All measures taken during in-lab sessions will be conducted on a laptop in the lab space. All measures taken during follow-up and online control sessions will be self-administered by participants via link to a Qualtrics survey.

*Primary objective measures—feasibility and acceptability of the intervention*
Feasibility: Number of eligible participants, willingness of participants to fully participate
(i)Rates of recruitment into the studyNumber of potentially eligible participants on SONA systems.Number of participants who completed the PHQ-9 screener and BDI-II item.Number (and proportion) of participants who were eligible to participate.Number (and proportion) of participants who were ineligible to participate at screening and why.Number (and proportion) of participants who consented to participate in intervention.Number (and proportion) of participants who scheduled the first in-lab session.Number (and proportion) of participants who completed the first in-lab session.(ii)Retention to treatmentNumber (and proportion) of participants who successfully completed all parts of the intervention (sessions 1, 2, and 3).Number (and proportion) of participants who drop out of the study and, when freely shared, reasons for drop out. In accordance with our informed consent, participants are free to drop out of the study at any point without explanation.(iii)Completion of between session tasks(iv)Number (and proportion) of participants who report needing to use their Coping Plan.(v)Number (and proportion) of participants who report using their Coping Plan when needed.(vi)Number (and proportion) of participants who report listening to their Self-Help recording in the week following the intervention session and 3 months following the intervention session.(vii)Number (and proportion) of participants who report listening to their Positive Future Memories recording in the week following the intervention session and 3 months following the intervention session.(viii)Attrition at post-treatment follow-up pointsNumber (and proportion) of participants who complete the 1-week follow-up questionnaire.Number (and proportion) of participants who complete the 1-month follow-up questionnaire.(ix)Levels of missing clinical outcome dataProportion of data completion for each questionnaire at each time-point.

Feasibility: Adherence/Compliance rates—Rating and adherence to intervention protocol. See above for details.

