### Progression criteria

Decisions regarding whether and how to proceed with testing this intervention on a larger scale are based on the feasibility and acceptability outcomes outlined above. Progression criteria are described in Table 2, following best-practice recommendations for progression criteria reporting [55].

**Table 2 Tab2:** Progression criteria

	Go: proceed with RCT	Amend: proceed with changes	Stop: do not proceed unless changes are possible
Feasibility of participant recruitment Can 60 participants be recruited who meet eligibility criteria (20 per group)?	If ≥ 12 participants can be recruited per month, 60 total	If ≥ 8 participants can be recruited per month, 40 total	If no participants can be recruited per month
Feasibility of participant retention Can ≥ 85% of participants be retained in the study until completion?	≥ 85% (95% CI*: 74–92%) retained through session 4 (1 week follow-up)	≥ 60% retained through session 4 (1 week follow-up)	< 60% retained through session 4 (1 week follow-up)
Intervention implementation Based on qualitative and quantitative data from both participants and experimenter	Delivery of intervention judged strongly feasible	Delivery of intervention judged feasible	Delivery of intervention judged possibly feasible
Feasibility of between-session tasks	≥ 60% participants complete between-session tasks	≥ 40% participants complete between-session tasks	< 40% participants complete between-session tasks
Feasibility of virtual reality medium (embodiment and engagement)	≥ 85% participants report acceptable ratings for avatar embodiment, engagement, and recognition	≥ 60% participants report acceptable ratings for avatar embodiment, engagement, and recognition	< 60% participants report acceptable ratings for avatar embodiment, engagement, and recognition
Acceptability of intervention Based on qualitative and quantitative data from both participants and experimenter	Intervention judged highly acceptable	Intervention judged acceptable	Intervention judged potentially acceptable

*Wilson interval calculated based on a sample of *n *= 60

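### The retention progression rule asks about retention to study completion but is judged at 1 week, so no threshold covers the 3-month visit, and the attrition outcome names a 1-month visit that is not scheduled

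*Protocol article*

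**What the plan says.** All places are in the Protocol article.

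- **Progression criteria, Table 2, retention row, question:** "Can ≥ 85% of participants be retained in the study until completion".
- **Same row, decision cells:** all three count participants "retained through session 4 (1 week follow-up"). Go is "≥ 85% (95% CI*: 74–92%) retained through session 4 (1 week follow-up"), Amend is "≥ 60% retained through session 4 (1 week follow-up") and Stop is "< 60% retained through session 4 (1 week follow-up"). The table footnote says that the interval is a Wilson interval for n = 60.
- **Study design and timeline:** follow-up is "at both 1-week and 3 months follow-up". Table 1 has the same two follow-up columns, f1 and f2, and no other. The Abstract gives the trial length as 4 months.
- **Table 1 and Outcomes measures:** the BDI-II, PIT and GSES are taken at baseline and at 3 months only.
- **Outcomes measures, feasibility item (viii), attrition:** one line for the 1-week questionnaire, then "Number (and proportion) of participants who complete the 1-month follow-up questionnaire". The 3-month questionnaire is not listed under this item.
- **Outcomes measures, feasibility item (ix), and Analyses, primary objective:** completeness of each questionnaire is reported by time point, and a CONSORT diagram shows when participants dropped out. Neither carries a threshold.

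**The concern.** The retention row does not answer its own question. It asks about the whole study and decides at the first of two follow-up visits. The interval between the two follow-ups is the longest wait in the schedule, so retention at 1 week says little about retention at the end.

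The uncovered visit carries much of the proof-of-concept objective. Depression on the BDI-II, vividness of future thought on the PIT, and self-efficacy have no other post-baseline value. The Research hypotheses expect effects to be strongest at 1 week and 3 months, and the growth-curve analysis is meant to show whether change continues after the intervention.

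The attrition outcome would be the natural place to pick up the later loss, but as written it points to a visit that nobody will hold. Table 2 serves the primary objective and decides whether a full trial follows. The pilot could therefore recommend that trial without having set the 3-month follow-up against any criterion.

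**Working it through.** **1. Where each statement points**

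| Statement | Time point |
|---|---|
| Table 2, retention question | study completion |
| Table 2, Go, Amend and Stop cells | 1 week |
| Attrition outcome (viii) | 1 week and 1 month |
| Study design and Table 1 | 1 week and 3 months |
| BDI-II, PIT, GSES after baseline | 3 months |

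The 1-month visit occurs only in the attrition outcome. The 3-month visit has no entry in that outcome and none in the decision cells.

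**2. Reproducing the stated interval**

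Inputs: 85% of 60 is 51, z = 1.96, p = 51/60 = 0.85, n = 60.

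Wilson limits = [p + z²/(2n) ± z·√(p(1−p)/n + z²/(4n²))] / (1 + z²/n)

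- Denominator: 1 + 3.8415/60 = 1.0640
- Centre: (0.85 + 0.0320)/1.0640 = 0.829
- Half-width: 1.96 × √(0.002125 + 0.000267)/1.0640 = 0.090
- Limits: 73.9% to 91.9%

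This rounds to the stated 74–92%, so the interval is correct for 51/60 over all arms.

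**3. What the rule can miss**

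The protocol gives no loss rate between 1 week and 3 months, so the further loss is an assumption, shown over a range. Start from Go just met (51/60 at 1 week). Retention at 3 months = 51 × (1 − further loss)/60.

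| Assumed further loss | 3-month retention | Table 2 as written | Same cuts applied at 3 months |
|---|---|---|---|
| 0% | 85.0% | Go | Go |
| 10% | 76.5% | Go | Amend |
| 20% | 68.0% | Go | Amend |
| 30% | 59.5% | Go | Stop boundary |
| 40% | 51.0% | Go | Stop |

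In whole participants, losing 15 of the 51 (29.4%) leaves 36/60 = 60.0%, the lowest Amend value. Losing 16 (31.4%) leaves 35/60 = 58.3%, which is Stop. The reading in Table 2 is Go in every line, because the later loss does not enter it.

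The room depends on the starting point. With all 60 retained at 1 week, 25 would have to be lost (41.7%) before 3-month retention fell to 35/60.

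**4. Effect of adding the 3-month cut**

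With the same 85% and the same 60 participants, the Go count is again 51 and the interval is again 73.9–91.9%. If 55/60 are retained at 1 week, Go at 3 months allows a further 4 losses (4/55 = 7.3%). If 60/60 are retained, it allows 9 (15%).

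**The case against.** The best defence is that 3-month loss is not ignored. Drop-out and completeness of each questionnaire at each time point are listed among the feasibility outcomes, and the CONSORT diagram will show losses by time point. The Progression criteria section says that decisions rest on the feasibility outcomes as a group. A reader might infer from Table 2 that 3-month loss would go unseen, and the documents do not support that. What remains is that no number is attached to it, while Table 2 does attach numbers to the 1-week visit.

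The 1-month wording is very probably a slip. The schedule, the objectives and other items in the same outcome list all say 3 months. That makes it easy to correct, but as written the outcome cannot be reported.

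It can also be said that BDI-II, PIT and GSES are secondary, that the pilot is declared unpowered for clinical effects, and that 1 week is itself an outcome time point. This limits the weight of the point. It does not reconcile the row's question with its cells.

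A reader might go further and infer that pooling the arms is an error and that retention should be judged in the 40 VR participants alone. The documents do not support this. A pooled rule is a common choice in a pilot, and nothing in the protocol says which arm will lose more. Go at 51/60 is met by 31/40 treated with 20/20 controls, but equally by 40/40 treated with 11/20 controls. A treated-only rule would read Go at 40/40 treated with 0/20 controls, where the pooled rule gives 40/60 = 67% and reads Amend.

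**Conclusion.** The point holds as a mismatch inside a primary-objective decision rule. The row asks about completion, decides at 1 week, and the supporting attrition outcome names a visit outside the schedule. Loss before the only post-baseline BDI-II, PIT and GSES is recorded but has no progression threshold.

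If Go is just met at 1 week, a further loss of about 30% brings 3-month retention to the table's own Stop boundary while the rule still reads Go. The 51/60 follows from the 85% and the n = 60 in the protocol. The 30% is an assumption, because no later loss rate is documented.

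Two stronger readings should be avoided. The stated 74–92% is not wrong: it reproduces for 51/60. Nor do the documents show that most 3-month depression data will be missing. From 51/60, having fewer than half of the 60 would need at least 22 of the 51 (43%) to be lost after week 1, and nothing in the protocol suggests that rate.

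**What to change.** - **Outcomes measures, feasibility item (viii):** change 1-month to 3-month.
- **Table 2, retention row:** apply the 85% and 60% cuts to completion of the 3-month follow-up as well as to session 4, over all 60 randomized. The interval of 74–92% at 51/60 stays as it is.
- **Reporting:** give retention by arm beside the pooled figure, as description and not as a separate criterion.

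The cost is the wording of one outcome line and one table row, with no new data collection. Go becomes somewhat harder to reach, since it must be met at the later visit too. The 85% and 60% cuts are carried over from the row itself, and the documents do not show that they suit a self-administered survey at 3 months. If the sponsor prefers other values for that visit, they should be fixed before the retention data are examined. Rewording the question to say 1 week would remove the contradiction but would leave the 3-month visit without a threshold.

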##### Sample size

As this trial is primarily to establish feasibility, acceptability, and proof of concept, a full power analysis is not appropriate. However, to be able to assess feasibility process outcomes, we target recruitment at sixty participants (*n* = 60), with *n *= 40 receiving the intervention. There is no consensus on sample size of pilot studies – recommendations range from 12 [31] to 50 [32]. This sample size of *n* = 60 is in line with multiple best practice recommendations for feasibility trials and it is suggested that a sample of 30 in the intervention arm is sufficient for the main aims of this pilot study: to adequately establish feasibility and to interpret qualitative measures of acceptability [33, 34].

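### No row of Table 2 isolates loss from the VR intervention: retention pools the controls, and the VR-medium and between-session rows state no denominator

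*Protocol article*

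**What the plan says.** All references are to the protocol article.

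- **Sample size.** The plan is "we target recruitment at sixty participants", with "40 receiving the intervention". Table 2 confirms equal groups: "Can 60 participants be recruited who meet eligibility criteria (20 per group". That makes 20 controls and 40 people allocated to VR (groups A and B).
- **Progression criteria, Table 2, VR medium.** The criterion is the percentage for which "participants report acceptable ratings for avatar embodiment, engagement, and recognition". Go is 85% or more, Amend is 60% or more, and Stop is below 60%.
- **Table 2, between-session tasks.** The criterion is the percentage of "participants complete between-session tasks". Go is 60% or more, Amend is 40% or more, and Stop is below 40%.
- **Table 2, retention.** Go is 85% or more through session 4, the 1-week follow-up. Amend is 60% or more, and Stop is below 60%. The footnote gives a Wilson interval on n = 60.
- **Study design and timeline, Table 1.** Engagement/embodiment and the line "Acceptability, feasibility, appropriateness" are marked for the experimental groups only, at t2 and t3. Intervention use is marked for the same groups at t3, 1 week and 3 months.
- **Outcomes measures.** Follow-up questionnaires are self-administered through an online link. The retention-to-treatment outcomes include the number and proportion of "participants who successfully completed all parts of the intervention (sessions 1, 2, and 3"). No row of Table 2 uses that outcome.

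**The concern.** Feasibility and acceptability are the primary objective, and Table 2 turns them into a decision. People who stop VR are the most direct evidence that it may not be feasible or tolerable, so the table should register them somewhere in undiluted form. It does not.

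Someone who leaves before t2 has no VR rating at all. If the VR-medium percentage is taken over the ratings in hand, that person is not counted. The retention row dilutes the loss with 20 controls who never face VR. It can also count as retained someone who stops VR but answers the 1-week questionnaire online. The outcome that would show the loss plainly, completion of sessions 1 to 3, is collected but has no threshold. The result is a decision that can lean towards Go, and the lean grows as more people stop.

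**Working it through.** **Reproducing the plan's own figure.** The Wilson 95% interval for 51/60 = 85% has centre (p + z²/2n)/(1 + z²/n) and half-width z√(p(1−p)/n + z²/4n²)/(1 + z²/n). With z = 1.96 and n = 60 it is 73.9% to 91.9%, which matches the printed 74–92%. The retention interval is therefore on all 60.

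**Can the VR row mean all 60?** Only 40 people can give a VR rating, so the ceiling is 40/60 = 66.7%. The 85% Go could never be met, and the denominator must be smaller. This argument does not carry over to the task row, where Go is 60% and 66.7% would pass. Coping Plan use is also listed among the between-session tasks, and all 60 receive that plan.

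**Loss scenarios.** The documents give no expected loss, so the number lost is an assumption, shown over a range. Let L of the 40 VR participants leave before any rating, with no control lost.
- Pooled retention = (60 − L)/60
- VR-arm retention = (40 − L)/40
- For the other two rows, take the smallest count that reaches Go among the 40 − L remaining, then divide the same count by 40.

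| L (of 40) | Pooled retention | VR-arm retention | VR row: remaining → of 40 | Task row: remaining → of 40 |
|---|---|---|---|---|
| 4 (10%) | 93.3% Go | 90.0% Go | 31/36 = 86.1% Go → 77.5% Amend | 22/36 = 61.1% Go → 55.0% Amend |
| 6 (15%) | 90.0% Go | 85.0% Go | 29/34 = 85.3% Go → 72.5% Amend | 21/34 = 61.8% Go → 52.5% Amend |
| 8 (20%) | 86.7% Go | 80.0% Amend | 28/32 = 87.5% Go → 70.0% Amend | 20/32 = 62.5% Go → 50.0% Amend |
| **9 (22.5%)** | **85.0% Go** | **77.5% Amend** | **27/31 = 87.1% Go → 67.5% Amend** | **19/31 = 61.3% Go → 47.5% Amend** |
| 10 (25%) | 83.3% Amend | 75.0% Amend | 26/30 = 86.7% Go → 65.0% Amend | 18/30 = 60.0% Go → 45.0% Amend |
| 16 (40%) | 73.3% Amend | 60.0% Amend | 21/24 = 87.5% Go → 52.5% Stop | 15/24 = 62.5% Go → 37.5% Stop |

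**How much depends on using the smallest count, at L = 9.**
- VR row: even 31/31 acceptable ratings give only 31/40 = 77.5%. Every Go among the remaining becomes Amend over 40.
- Task row: 24/40 = 60% is Go. Only counts from 19 to 23 change category; 24 to 31 read Go either way.

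**Where retention hides the loss.** With no control lost, pooled retention reads Go up to L = 9, because 51/60 = 85%. VR-arm retention falls below Go from L = 7, because 33/40 = 82.5%. The hidden window is therefore 7 to 9 losses. Each control lost takes one off its upper end.

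**The case against.** The strongest reply is that drop-out already has its own row. Session 4 comes after both VR sessions, so anyone who leaves the study earlier fails retention. A reader might infer that a programme losing 40% of its VR users would still read Go. The documents do not support that. If 16 of 40 leave the study, retention is 44/60 = 73.3% with no control lost, or 36/60 = 60% if controls leave at the same rate, and both read Amend. Retention could read Go in that case only if people who stop VR still answer the 1-week follow-up.

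A reader might also infer that the plan excludes people who stop. It does not say so. That is one reading of an unstated denominator, and the 40 allocated is another.

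Other points that stand:
- Someone who leaves after the first VR session has already given a t2 rating, so only losses before t2 are wholly absent from the VR row. Table 2 does not say which session's rating counts.
- Task completion is self-reported use, and the 1-week and 3-month questionnaires can still collect it from someone who has stopped VR. With 24 remaining and all completing, 24/40 = 60% is Go even on the full denominator.
- The implementation and acceptability rows draw on the experimenter as well as participants, and drop-out and questionnaire completion will be reported. Judgement could pick up the loss.
- Scoring a person who never entered VR as failing embodiment mixes attendance with realism, and it counts one loss in several rows.

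It can also be said that denominators belong in a fuller document. That is fair for analysis detail, but the decision rule is printed here with its cut-points, and the retention row does state its n. The lack of a VR-completion criterion and the pooling of controls do not depend on any unshown detail.

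**Conclusion.** The point holds in a limited form. Table 2 contains no criterion that isolates loss from VR. The retention row pools controls and counts reaching an online follow-up, and the VR-medium and between-session rows fix neither a denominator nor a rule for missing data.

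With 7 to 9 of 40 lost and no control lost, the retention, VR-medium and task rows can all read Go, while over the 40 allocated all three can read Amend. At 9 lost the pairs are 85.0% against 77.5%, 87.1% against 67.5%, and 61.3% against 47.5%.

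This rests on three assumptions: the losses occur before any rating, no control leaves, and the two rows are computed among those remaining. The change is from Go to Amend, that is, from proceeding to proceeding with changes. The Stop readings at 40% loss concern the VR and task rows taken alone, not the table as a whole.

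**What to change.** In Table 2:

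1. Add a row for the share of all participants allocated to groups A and B (planned n = 40) who completed both VR sessions, with the 85% and 60% cut-points the table already uses.
2. State the denominator of the VR-medium row, and of the recording-task part of the between-session row, as those 40. Count a missing rating or report as not met.
3. Print the among-attenders percentage beside each, so that the quality of the VR experience can be read separately from attendance.

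The first item does most of the work and avoids the debate about scoring people who gave no rating. The cost is wording only, since session completion, ratings and use reports are already collected. The downside is that the reported percentages become less favourable, and some losses unrelated to VR will count against it.
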